#### Secondary outcome measures

Secondary outcomes will be multidimensional frailty, physical phenotype of frailty, feeling frail, balancing factors (i.e., resilience, coping, help needed for activities in daily life, informal and formal care, medical care, leisure time, neighborhood), future perspective and life-events.

The Comprehensive Frailty Assessment Instrument (CFAI-plus) will measure *multidimensional frailty* [12, 50]. The physical domain evaluates the general physical health (e.g., walking up a hill or stairs); the psychological domain assesses mood-disorders and emotional loneliness (e.g., feeling pressure); the social domain contains social loneliness and social support (e.g., there are enough people I feel close to); and the environmental domain evaluates conditions of inadequate housing using (e.g., my house is in a bad condition). Cognitive frailty was recently added to the CFAI and evaluates cognitive functioning (e.g., memory problems) [50]. The Fried’s phenotype of frailty (slow mobility, weakness, weight loss, decreased activities and exhaustion) [7] will be used to assess the physical phenotype of frailty as well as the questionnaire of Op het Veld et al. [51]. For weakness and slow mobility, 180 older participants will do the physical tests included in the Fried’s phenotype of frailty. The *subjective feeling of frailty* will be assessed with a self-constructed question which explores to what extent the participant agrees with the statement ‘I feel frail’. Older participants will also be asked to rate their subjective feeling of being frail on a scale from 0 to 10. *Resilience* will be measured by using the Connor-Davidson Resilience Scale (CD-RISC2), which is an abbreviated 2-item version of the original Scale [52]. *Coping* will be measured by using 6 items (i.e., active coping, positive reframing, acceptance, religion, emotional support and self-distraction) of the BRIEF Cope Carver scale [53]. By proposing statements, older participants need to answer to what extent they would react like this in a stressful or difficult situation. *Help needed for activities in daily life* will be measured by asking if older participants need help with 8 activities of daily life (i.e., personal care, household tasks, personal displacements, administrative and financial management, social company and support, grocery shopping, chores and supervision), and to what extent the help they receive for these activities is sufficient. These questions are adapted from the questionnaire of the Belgian Ageing Studies (BAS) [54]. *Informal and formal care* will be assessed by asking older participants if they receive care from 7 informal (e.g., children, neighbors, friends) and 13 formal caregivers (e.g., home nursing), and if they are satisfied with the help they receive from these caregivers. These questions are adapted versions of the BAS-questionnaire [54]. *Medical care* will be measured by asking how many times the participants needed to go to a general practitioner, a hospital, residential setting and/or rehabilitation center over the past 6 months (day care/overnight stay). These questions are adapted from the Health Interview Survey [55]. In addition, the participants will be asked when they visited a general practitioner for the last time. Also different aspects of the environment will be assessed. First, the *social environment* will be administered by using 3 items from the social cohesion dimension of the Neighborhood Scale [56]. Second, the *physical environment* will be explored by using 4 items from the BAS-questionnaire [54] as well as from the Neighborhood Environment Walkability Scale [57]. In terms of *participation*, leisure time will be measured by using an adapted question with 8 items derived from the BAS questionnaire [54]. This question will examine how often the participants perform following activities: giving care or support, voluntary work, activities at home, sport activities outside a club, cultural activities, activities in an organization, going to a bar/restaurant/shopping center/trips, attend training. Also, low-key social participation will be examined by using 2 items from the questionnaire of Oswald and Konopik [58]. *Future perspective* will be assessed by using a self-constructed question and will explore to what extent the participant has things to look forward to. Finally, the occurrence of *life-events* will be assessed by using a shortened version (11 items) of the Geriatric Adverse Life Events Scale (GALES) [59, 60].

#### Additional measures

Several variables will be assessed in order to provide insight information concerning the study population, and to interpret outcomes of the study. These are the socio-demographic variables, assessed during the process of screening for eligibility: age, gender, country of birth, educational level, marital status and moved last 10 years [29, 54]. Additionally, also nationality will be assessed as well as the socio-economic situation (net monthly household income) [54].

The questionnaires will be available in Dutch and in French. Questions from existing instruments will be translated (if not already validated in the respective language) using a team translation approach called the Translation, Review, Adjudication, Pre-Testing and Documentation (TRAPD) translation model [61]. Team approaches provide the richest output in options to choose from for translation. Another advantage of this method is the acquisition of balanced critique and a more fundamental choice between different versions [62]. In the TRAPD model, several translators will make independent parallel translations of the same questionnaire [61]. Thereafter, the translators and translation reviewers will go through the entire questionnaire discussing versions and agreeing on a final review version. The version produced trough discussion will move on to adjudication. The survey will also be screened by “Wablieft”, an organization who will check the accessibility and clarity of the survey taking into account the target group, (possibly frail) older adults.

#### Process evaluation

In order to evaluate the quality and sustainability of the D-SCOPE frailty program a quantitative questionnaire will be used during the intervention to measure the number of older adults that participated in the second home visit (1), started the intervention (2) and, dropped-out during the intervention (3). A professional from the social service of each municipality will also keep track of a logbook. In this logbook the amount of contacts in the intervention, the offered informal and formal care and support, satisfaction about the offered care and support and the problems encountered during the intervention will be registered. The reasons for refusal/dropout before the start as well as during the intervention will be evaluated as well.

In addition, after T1, in each municipality 3 focus groups will be organized: one with older adults who participated in one of the four groups, one with informal caregivers and one with professionals participating in the D-SCOPE frailty program. Because in complex interventions social or behavioral processes are difficult to explore using quantitative methods alone [63] the use of an additional qualitative research design will be helpful in providing valuable new insights. The goal is to determine the participant’s opinions concerning the added value of the program and to identify components that support or inhibit the process of implementing the D-SCOPE frailty program. The focus groups will be held by a semi-structured interview schedule, developed following a literature review and input from the D-SCOPE consortium, consisting of researchers from different research areas from different universities:Satisfaction with the D-SCOPE frailty programExperiences of the care/support processesIdentification of components that support or inhibit the process of implementing the D-SCOPE frailty program: the extent to which success factors or problems were encountered while applying the program.

#### Data gathering

Data on baseline characteristics, frailty, balancing factors and outcomes will be collected to evaluate the effect of the intervention with questionnaires at two points in time: T0 and T1 (6 months after inclusion). Participants in the study will concern all groups; the experimental group of the RCT, the control group of the RCT, older participants with no-to-low frailty (CFAI-plus) or who do not feel frail (subjective assessment of frailty) and care avoiders. Trained volunteers or researchers will collect the T0 data. A professional from the social service of the municipality will receive all completed questionnaires and informed consents from the baseline assessment after the first home visit and will register the completed questionnaires in a specific designed computer program named Qualtrics. The research coordinator, who is responsible for the randomization to the control and experimental group, will be the person who can consult the results and will communicate to the municipality which respondents are randomized in the experimental group. The municipality will arrange that the experimental group receives a second home visit by a professional from the social service of the municipality, search an appropriate intervention and do the follow-up. After 6 months, trained volunteers and researchers will collect the T1 data. A professional from the social service of the municipality will again receive all completed questionnaires from the T1 assessment and will register them in the specific designed computer file. At the end, the research coordinator will consult the data.

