**Fig. 1 Fig1:**
[figure not shown]
Flow diagram of the D-SCOPE frailty program

Older adults who are at least mild frail on one of the 5 domains of frailty (CFAI-plus) or feel frail based on the subjective assessment of frailty will be randomly assigned to either (1) the experimental group or (2) the control group. Older adults with no-to-low frailty (CFAI-plus) or who do not feel frail (subjective assessment of frailty) will be grouped into a third group. A fourth group will include frail older adults willing to participate in the T0 and T1 assessment but not in the intervention part. All groups except for the experimental group will receive care as usual.

All older participants will be assessed after a 6 months’ period. The study will include an effect evaluation and a process evaluation of the RCT. The effect study will be conducted using a quantitative evaluation of the outcome measures for frail community-dwelling older adults. The process evaluation will be performed by a quantitative monitoring of the experimental group (including follow-up telephone interviews) and qualitative focus groups with older adults, informal caregivers and municipal health and social care professionals in each municipality.

The baseline assessment T0 will begin in June 2017 until October 2017. The study assessment T1 will begin in December 2017 until April 2018. The intervention will take place between June 2017 and March 2018, between the baseline assessment T0 and the study assessment T1. The qualitative evaluation will take place in March and April 2018. The data analysis will take place between April 2018 and June 2018.

The content of the program has been developed in close collaboration with representatives of different home care and support levels, i.e. general practitioners, home care organizations, social service of the municipalities, home nurses, older people’s organizations, centers of expertise in housing and care, care insurances companies, universities, etc.

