#### Blinding

Older participants, interviewers performing the baseline assessment and researchers doing the outcome assessment and data analysis will be blinded to group allocation. It won’t be possible to blind the research coordinator and municipal health and social care professionals performing the intervention to group allocation. Interviewers won’t be blinded when doing the follow-up.

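### All T0 and T1 questionnaires, controls' included, pass through the municipal service that delivers the intervention, with no stated safeguard against contamination of the control arm

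*Protocol article*

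**What the plan says.** All of this is in the Protocol article.

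- **T0 forms (Data gathering).** "A professional from the social service of the municipality will receive all completed questionnaires and informed consents from the baseline assessment". This professional also registers them in the survey program.
- **T1 forms (Data gathering).** A professional of the same service "will again receive all completed questionnaires from the T1 assessment and will register them".
- **Whose forms (Data gathering).** "Participants in the study will concern all groups; the experimental group of the RCT, the control group of the RCT", and then the two non-randomised groups. Controls are not excepted.
- **Who learns the allocation (Data gathering).** The research coordinator "will communicate to the municipality which respondents are randomized in the experimental group".
- **Who delivers (Data gathering; Intervention).** "The municipality will arrange that the experimental group receives a second home visit by a professional from the social service of the municipality". The service's professional uses the T0 results and the second visit to propose care, and then follows the participant by monthly telephone calls.
- **Blinding.** The article says that it will not be possible to "blind the research coordinator and municipal health and social care professionals performing the intervention to group allocation".
- **Control condition (Study design, text after Fig. 1).** "All groups except for the experimental group will receive care as usual".

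Data gathering also names the research coordinator as the person able to consult the results. The article does not separate the staff who enter data from those who deliver care, and it does not say that controls' forms are masked from the service.

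**The concern.** The programme's first aim is to find frail older people who lack the care they need and guide them to it. The T0 questionnaire is the detection tool. It records frailty in five domains, help needed in eight daily activities, whether that help is sufficient, and the informal and formal care received (Secondary outcome measures). Sending every control's form to the delivering service gives that service the detection information for both arms. If it acts in good faith on what it sees, some controls get part of what the trial is testing, and the estimated effect moves towards zero.

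The T1 route raises a second, lesser issue. All six primary outcomes come from these questionnaires, and they are entered inside the organisation that delivered the intervention and was told the allocation. Any bias from this would more plausibly favour the programme, so the two risks need not point the same way.

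**Working it through.** **1. Can the service identify controls?** The allocation message names only the experimental group. Non-frail participants and those who decline the intervention are also absent from that list, so absence alone does not mark a control. The RCT comprises people who meet a frailty cut-off or feel frail and who accept the intervention (Participants and eligibility criteria). Someone holding the T0 forms and consents could therefore work out control status: frail on the form, willing to take part in the intervention, not on the list. This takes some effort but is possible.

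**2. Which wave carries which risk?** Randomisation follows the baseline assessment (Randomization), so T0 answers are given before allocation. The T0 issue is knowledge of controls' needs. Handling of outcomes with knowledge of allocation can arise only at T1.

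**3. Does the service need these forms?** Its stated intervention tasks are the second visit, proposing and arranging care, accompanying the referral and monthly monitoring. These need T0 results for the experimental arm. Apart from data entry itself, no stated task needs a control's form or any T1 form.

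**4. The plan's own power figures.** Two-sample t-test, two-sided alpha 0.05 (sidedness is not stated, but two-sided reproduces the figures), power 0.80:
- d = 0.5: 63.8, rounded up to 64 per group (stated: 64).
- d = 0.2: 393.4, rounded up to 394 per group (stated: 394).
- Cited study, 220 per arm less 10% loss: 220 × 0.90 = 198. At d = 0.3 the power is 0.846 (stated: 0.837); at d = 0.5 it is 0.999 (stated: 0.997). Both are close.

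**5. Illustration of dilution.** Assume that a share c of controls receives the full benefit and that the standard deviation is unchanged. The control mean rises by c × d, so the observable difference is d × (1 − c). For a true d of 0.30:

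| c (assumed) | Diluted d | Power at 198 per arm | n per arm for 80% power |
|---|---|---|---|
| 0 | 0.30 | 0.846 | 176 |
| 10% | 0.30 × 0.90 = 0.27 | 0.764 | 217 |
| 20% | 0.30 × 0.80 = 0.24 | 0.664 | 274 |
| 30% | 0.30 × 0.70 = 0.21 | 0.550 | 357 |

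Hand check with the normal approximation, power ≈ Φ(d√(n/2) − 1.96), where √(198/2) = 9.95. For d = 0.27: 2.69 − 1.96 = 0.73, giving about 0.77. For d = 0.24: 2.39 − 1.96 = 0.43, giving about 0.67.

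If a contaminated control gets only a fraction b of the benefit, the factor is 1 − c × b. Half the benefit in 20% of controls (1 − 0.20 × 0.5 = 0.90) equals the 10% row.

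**The case against.** **Same person?** A reader might infer that one individual both enters the data and delivers care, or that whoever enters T1 data knows each participant's arm. The article does not say so. It speaks of a professional of the service, and its blinding statement covers municipal professionals who perform the intervention. The point therefore holds for the service, not for a named role. It still stands, because no separation inside the service is stated.

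**Will the service act?** That it will help controls, or has a stake in the result, is also inference. The text supports only that it is in a position to act.

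**Access limit.** The sentence on who can consult the results may be meant as a safeguard. It cannot cover completed forms that the service has already received and keyed in. A condensed article may well leave coding and staffing detail to a fuller protocol, but the routing itself is stated here and is not an omission.

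**Entry bias.** This objection largely stands. The primary outcomes are participants' own answers, collected by volunteers and researchers. Registering them is transcription, so bias would need altered or selectively miskeyed answers, and entries can be checked against the forms. The article also says that follow-up interviewers are not blinded, which is a more direct threat to the same outcomes. The added risk from municipal entry is probably small.

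**Correctable in analysis?** Informal and formal care are recorded at T0 and T1 in all groups, so contamination can be partly observed. Describing it does not restore the randomised contrast.

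**The numbers.** The contamination rates have no source in the documents. One contact prompted by a form is unlikely to equal a second visit, tailored care, accompanied referral and monthly calls, so full benefit is a pessimistic assumption. Both 198 per arm and d = 0.30 come from the cited study; this trial's 900 are spread over four groups and no number per randomised arm is fixed.

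**Conclusion.** The point holds as a flaw in the stated data flow. The service that delivers the intervention and learns the allocation also receives and registers every participant's T0 and T1 questionnaire, controls included, and no internal separation is stated. The main consequence is an avoidable opening for contamination through the T0 forms. Entry of T1 outcomes in the same organisation is a secondary and probably small concern.

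The size cannot be derived from the documents. Under the labelled assumptions (10-20% of controls receiving full benefit, true d of 0.30, 198 analysed per arm, two-sided 5%), d falls to 0.27-0.24 and power from 0.85 to 0.76-0.66. This shows sensitivity and is not a forecast. The documents do not support a claim that contamination will occur, that outcomes will be mis-entered, or that the net bias has a known direction. The change is worth making because the opening serves no stated purpose beyond data entry and is cheap to close.

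**What to change.** Change the data-flow text and the access rights as follows.

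1. **T0:** the interviewers enter the forms in the existing survey program, or return forms and consents to the research team.
2. **After randomisation:** release T0 results to the municipality for the experimental arm only.
3. **T1:** return forms to the research team for entry by researchers blinded to allocation. Do not route them through the municipality, and do not have the follow-up interviewers enter them, since the article says these are unblinded.
4. **Reporting:** use the care-use items collected at T0 and T1 to describe, by arm, any contamination of the controls.

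The cost is that data-entry work moves from municipal staff to staff already on the study. Sample size, outcomes and the intervention are unchanged. The unblinded follow-up interviews are a separate matter that this change does not solve.

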#### Power analysis

As we have no clear view yet on all aspects, factors, scales, outcomes, statistical analyses, etc., it is not feasible to run detailed power analyses a priori. However, according to Cohen [64] and when using the online a priori sample size calculator for independent sample t-tests [65]; the minimum sample size per group (experimental as well as control group) with a probability level of .05, an anticipated Cohen’s d effect size of 0.5 (medium) and a desired statistical power of 0.8 will be 64. To find differences with a small effect size (cohen’s d = 0.2) between the 2 groups a total n of 788 (394 in each group) is required.

As is our longitudinal design is concerned, we have based our a priori estimation on a study of Fabricotti et al. [66]. They expect a 10% loss to follow up (due to mortality, re-housing, impossibility or unwillingness to participate further) between T0 and T1. By including 220 older adults in both the experimental and control group, they state that their sample is sufficient to detect changes. Assuming an average effect size of 0.5 and significance of 5%, this gives a power of 0.997. They further argue that if a small effect size is expected of 0.3 with a significance of 5%, this still supplies sufficient power at 0.837. Interfering variables will also play a role. At an average effect size (f2) of 0.15 and significance of 5%, assuming five independent variables, the power is 0.97. Even with 15 independent variables, the power remains sufficient at 0.856.

So, in sum, it was decided to aim for 900 community-dwelling older adults aged 60 years, equally divided over the municipalities Knokke-Heist, Ghent and Tienen in Flanders, Belgium; so 300 community-dwelling older adults will participate in each municipality.

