## Background

Frailty is a common phenomenon in community-dwelling older adults. Research indicates that the average prevalence for multidimensional frailty is 13.6% and 33.5% for prefrailty in community-dwelling older adults [1]. Frailty increases with age [1, 2]. For example, a systematic review on the prevalence of frailty indicates that the prevalence for oldest-old people is 15.7% (80–84 years) and 26.1% (≥ 85 years) [1]. Within an aging society, more and more persons are confronted with frailty and the demand for care and support increases [3–6]. Although frailty has mainly been approached as a physical issue [7, 8], different researchers point to the necessity to operationalize frailty as a multidimensional and dynamic concept that considers the complex interplay of physical, cognitive, psychological, social and environmental factors [9–12]. Not only researchers identify frailty in a multidimensional way, older adults themselves experience frailty as more than merely a physical issue as well [13].

As older adults become frail, different dimensions of their lives such as their quality of life and feelings of control (e.g. mastery) may be affected [14–16], and their risk for adverse outcomes such as hospitalization and institutionalization increases [17–19]. A study by Rockwood et al. [19] indicates that frailty is one of the most important predictors of death and institutionalization. Governments are implementing a proactive care approach in order to prevent or delay (the high costs of) such institutionalization and other adverse outcomes, and stimulate older adults to stay in their own environment as long as possible with good quality of life [20]. This so-called policy on aging in place is in line with the wish of the majority of older adults [21], even when they need care and support, have economic difficulties or live in inadequate housing or deprived environments [22].

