### Participants and eligibility criteria

Study participants will be community-dwelling older adults aged 60 years and over. In order to explore the most efficient selection strategy to detect frail older adults, two randomized selections, with replacement addresses, from the census records will take place in each municipality. Each randomized selection in each municipality will include 150 participants. The two stratified samples will be based on previous research on risk profiles for frailty [29]**.** Risk characteristics for frailty are gender, age, marital status, moved in the past 10 years and migration background. In the first sample (*n* = 450) older participants will need to fulfill at least one criterion. This implies that the participants will be women or aged 70 years and over or not have a partner or have moved in the past 10 years or will have a migration background. In the second sample (*n* = 450) all older participants will need to fulfill all selection criteria. This implies that older participants will be aged 70 years and over, have no partner, and moved last 10 years. The second sample will exclude the variable migration background due to too small samples within the three selected municipalities.

Exclusion criteria will be current hospitalization, institutionalization, when the older participant himself or his/her informal caregiver indicates that the older participant is not able to participate or if the interviewer notes that the older participant is cognitively not capable to provide adequate answers.

Older adults will be included in the RCT if they are at least mild frail on one of the 5 domains of the CFAI-plus (i.e., ≥ 25 for physical frailty, ≥ 12.52 for cognitive frailty, ≥ 20 for psychological frailty, ≥ 37.5 for social frailty and ≥ 5 for environmental frailty) or feel frail based on the subjective assessment of frailty (i.e. at least agree with the statement), and accept to participate in the intervention.

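### The target of 900 counts everyone assessed at baseline in all four groups, but the two-arm power figures it is drawn from need a number randomised, which is never given

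*Protocol article*

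**What the plan says.** All references are to the protocol article.

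- **Power analysis**, first paragraph: for a two-group t-test at the 5% level with 80% power, 64 per group for d = 0.5 and 394 per group (788 in total) for d = 0.2.
- **Power analysis**, second paragraph: figures taken from a cited study with 220 in each of the experimental and control groups and 10% expected loss. Power is 0.997 at d = 0.5, and "if a small effect size is expected of 0.3 with a significance of 5%, this still supplies sufficient power at 0.837". Regression powers at f² = 0.15 follow: 0.97 with five independent variables, and "Even with 15 independent variables, the power remains sufficient at 0.856". No N is attached to the regression figures.
- **Power analysis**, conclusion: "it was decided to aim for 900 community-dwelling older adults aged 60 years, equally divided over the municipalities".
- **Participants and eligibility criteria**, on how the 900 arises: "Each randomized selection in each municipality will include 150 participants". Two selections of 150 in three municipalities make 900, set before frailty is measured.
- **Participants and eligibility criteria**, on who is randomised: "Older adults will be included in the RCT if they are at least mild frail on one of the 5 domains of the CFAI-plus" or feel frail, "and accept to participate in the intervention".
- **Study design**: people with no-to-low frailty "will be grouped into a third group", and frail people who want the assessments but not the intervention form a fourth. Neither is randomised. Data gathering counts all four groups as study participants.

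**The concern.** The sample-size argument starts from two randomised arms and ends with a total over four groups, two of which contribute nothing to the randomised comparison. The conclusion therefore does not follow from the premises. The number that determines power is whatever remains of the 900 after two filters, being frail (or feeling frail) and accepting the intervention. The article gives no expected value for either.

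At stake is whether the trial can detect the smaller effects the section discusses. The effect it labels medium is safe over a wide range of shares. For d = 0.2 and 0.3, power depends heavily on the unstated share, and a reader who sets 788 beside 900 cannot tell how far apart they are in randomised terms.

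**Working it through.** **1. Reproducing the stated group sizes.** Two-sample t-test, two-sided 5% level, 80% power. The normal approximation is n = 2(1.96 + 0.8416)²/d².
- d = 0.5: 15.70/0.25 = 62.8; with the noncentral t, 63.8, so 64 per arm. Reproduces.
- d = 0.2: 15.70/0.04 = 392.4; with the noncentral t, 393.4, so 394 per arm. Reproduces. No loss is included.

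**2. Reproducing the stated t-test powers.** 220 per arm less 10% is 198. The noncentrality is d√(n/2). At d = 0.3 it is 0.3 × √99 = 2.985, and the normal approximation gives Φ(2.985 − 1.96) = 0.847. With the noncentral t:
- d = 0.5: 0.999 (stated 0.997).
- d = 0.3: 0.846 (stated 0.837).

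Both are within 0.01, so these two figures are not in error for the design they are attached to.

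**3. From arms to a share of the 900.** Equal allocation is assumed, as the per-group figures imply.

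| Needed | Per arm | Total randomised | Share of 900 |
|---|---|---|---|
| d = 0.5, after 10% loss | 64/0.9 → 72 | 144 | 16.0% |
| Size in the cited study | 220 | 440 | 48.9% |
| d = 0.2, no loss | 394 | 788 | 87.6% |
| d = 0.2, after 10% loss | 394/0.9 → 438 | 876 | 97.3% |

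The last row leaves 900 − 876 = 24 people for the non-frail group and the decliners together, over three municipalities.

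**4. Power by randomised share.** The share is an assumption, so a range is shown. Analysed n per arm = 900 × share / 2 × 0.9; two-sided 5%.

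| Share randomised | Analysed per arm | d = 0.2 | d = 0.3 | d = 0.5 | Detectable d at 80% |
|---|---|---|---|---|---|
| 30% | 121.5 | 0.34 | 0.64 | 0.97 | 0.36 |
| 40% | 162 | 0.43 | 0.77 | 0.99 | 0.31 |
| 48.9% | 198 | 0.51 | 0.85 | >0.99 | 0.28 |
| 50% | 202.5 | 0.52 | 0.85 | >0.99 | 0.28 |
| 60% | 243 | 0.60 | 0.91 | >0.99 | 0.26 |
| 80% | 324 | 0.72 | 0.97 | >0.99 | 0.22 |
| 100% | 405 | 0.81 | 0.99 | >0.99 | 0.20 |

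**5. The regression powers.** Overall F-test of k predictors, noncentrality f² × N, k and N − k − 1 degrees of freedom, f² = 0.15.

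| Total N | k = 5 (stated 0.97) | k = 15 (stated 0.856) |
|---|---|---|
| 154 | 0.971 | 0.856 |
| 396 (198 per arm) | >0.999 | >0.999 |
| 440 (220 per arm) | >0.999 | >0.999 |

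The stated values match a joint test of all predictors at a total N of 154. They do not match 220 per arm, with or without the 10% loss. The Effect evaluation part of the analysis section names research group as the variable of interest, which is a one-degree-of-freedom question and not a joint test. For two equal arms f² = d²/4, so f² = 0.15 for the arm effect alone would mean d = 2√0.15 = 0.77, larger than any effect the section considers.

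**The case against.** Several points can fairly be made for the plan.

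- *Power is ample for d = 0.5.* This stands: randomising 30% of the 900 still gives 0.97.
- *The article admits that a detailed power analysis was not possible.* True, but it then gives a numerical argument and draws a target from it. The objection is to that inference, not to missing detail.
- *The sample is selected on risk, and entry is broad (any one of five domains, or feeling frail), so the randomised share may be high.* This stands as a reason not to fix on a low share. The Background states that "the average prevalence for multidimensional frailty is 13.6% and 33.5% for prefrailty", which adds to 47.1%, or 424 of 900 before decliners are removed. That is a general community average under other definitions, and it should not be taken as this trial's expected share. The first sample, on the other hand, requires only one risk characteristic. The uncertainty in both directions is why the assumption needs stating.
- *The regression powers are too low for 220 per arm, so they mislead no one into a smaller trial.* This stands and keeps that point secondary.

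Two stronger readings are tempting. First, 0.997 and 0.837 also match, to three decimals, a one-sided test at 154 per arm, which is 70% of 220. A reader might infer that the section mixes one- and two-sided tests, or 10% with 30% loss. The article states none of this, the figures come from a study not at hand, and they agree acceptably with 198 per arm two-sided. Second, a reader might infer that the article claims d = 0.2 is covered. It says only that 788 would be required; it attaches sufficiency to 0.3.

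**Conclusion.** The concern holds for the link between 900 and the randomised comparison. The 900 is a baseline total over four groups, the t-test figures describe two arms, and no section joins them. The 220 per arm is within reach but depends on nearly half of all those assessed (48.9%) being both eligible and willing. The 394 per arm for d = 0.2 would need 87.6%, or 97.3% with 10% loss, which is implausible in a design that sets up a non-frail group and a decliner group. Power for d = 0.3 runs from about 0.64 to 0.97 as the share goes from 30% to 80%.

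These results assume equal allocation, individual-level t-tests, a two-sided 5% level and 10% loss; the shares are illustrative. The quoted t-test powers stand. The regression powers are misplaced, since they belong to a different N and a different test, but conservatively so. A null result could still be read through its confidence interval; what is missing is a planned detectable effect for the number actually randomised.

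**What to change.** Rewrite the Power analysis section:

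1. State the target as the number randomised, with the assumed frail (or feeling frail) fraction and the assumed accepting fraction that lead from 900 to it.
2. Give two-sided power and the detectable effect over a range of analysed numbers per arm, as in the table above. At 198 per arm: 0.85 for d = 0.3, 0.51 for d = 0.2, detectable d of 0.28 at 80% power.
3. Say plainly that d = 0.2 is not powered at any plausible randomised share.
4. Remove the f² powers, or recompute them for the arm effect at the expected analysed N.

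The cost is one rewritten section and a less favourable stated power for small effects. No extra participants are needed.
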